### Blinding

It is not possible for the midwife delivering the intervention to be blinded to the pregnant women in the intervention groups or the usual antenatal care group. Also, the principal researcher will not be blinded to the participants to be invited in the interviews post-intervention. However, the principal researcher, who will be conducting baseline and follow-up data analysis, will be blinded to the allocation when analysing the feasibility data.

### Interventions

The participants in the intervention group will receive PFMT supervision in groups of eight women. The intervention will include verbal instruction on PFMT, the use of models and pictures of the pelvic floor to help women identify their pelvic floor muscles and then guide them on how to contract the pelvic floor muscles correctly. The content of this PFMT programme was adapted from a published protocol [34] and co-designed with stakeholders to suit the needs of a different population (pregnant women) and setting (Nanjing city) as recommended by the MRC framework [18]. The stages in co-designing the group-based PFMT programme are described in Additional file 2. In brief, the exercise includes three repetitions with 2-min rests between each repetition. One repetition comprised eight contractions with each held for 6 s, followed by three or four fast contractions. Learning and practising the exercise will be supervised in the group sessions and will be required to be repeated twice per day at home between group sessions.

All the group-based training sessions in the programme will be provided by one midwife to ensure consistency. The midwife will be trained beforehand by the principal researcher about the PFMT programme. The participants will be required to meet the midwife for group supervision once a month on the day of their regular antenatal check for consecutive four consecutive months (approximately 24 gestational weeks, 28 gestational weeks, 32 gestational weeks and 36 gestational weeks). The group supervision sessions will last for about 45 min which include attendance registration and progress review (5 min), education on the causes of UI and PFMT (10 min), skills training in sitting and standing positions (20 min), discussion on what is taught (8 min) and reminder about the next session (2 min). The registration of attendance and the training diary which will be provided to the participants after each session will be monitored to record adherence to the programme. Women who attend at least 75% of the supervision sessions will be considered as adherent. Motivation to maintain PFMT will be emphasized by the midwife and supported by WeChat groups which will be limited to the eight pregnant women in the group session. A reminder to practise PFMT as well as the audio instructions on doing PFMT will be sent automatically in the WeChat group twice a day. In addition, leaflets on PFMT, training diaries and stickers which motivate the participants to undertake PFMT will be provided. The PFMT leaflets and training diary were provided as Additional file 3. One day before the next session, a reminder of the session date will be sent to the WeChat group. The participants will be encouraged to discuss any topics related to PFMT and UI in the WeChat group to facilitate peer support. The midwife and the principal researcher will adopt administrative roles and monitor the WeChat groups but will not answer questions or participate in discussions. Any problems which the pregnant women encountered during the exercises will be addressed during face-to-face supervision. There will be ground rules set for the groups, for example, the women in the groups need to keep the information confidential within the group and treat each woman in the group with respect. If any women break the ground rules or discuss information in the WeChat group that is unsafe, the principal researcher will remind the women about the ground rules and correct any information that is dangerous. During the development of this study, the barriers identified from the systematic review [13], survey [24] and discussion with stakeholders, such as time commitment, forget to continue PFMT were mapped to the COM-B model and explored in a separate study. For reasons of equipoise, women in the comparator group will be offered the group-based PFMT intervention at the end of the study if they wish.

### Comparator

The comparator is usual antenatal care, which means the participants will receive verbal instruction on PFMT from midwives without any further supervision. The participants receive instructions on standard antenatal practice, such as eating, sleeping, nursing newborn babies for the purpose of preparing for delivery and the postnatal period. The participants will not be discouraged from performing PFMT for ethical reasons.

### Measures

The outcomes will involve both qualitative and quantitative outcome measures. One focus group interview with the participants and one semi-structured interview with the midwife who delivered the intervention will be held by the principal researcher in an office in the antenatal clinic. The midwife will not be involved in the focus group interview with the participants. The focus group interview aims to assess the acceptability of randomization, the outcome measure and the intervention. About six to eight participants will be purposively sampled from the intervention groups which means the participants were selected based on the researcher’s own judgement. The principal researcher aimed to select participants including both women who strongly adhered to the training programme and women who did not attend at least three face-to-face sessions. Compared to the other sampling approach, purposive sampling can better match the sample to the aims and objectives of the research [35]; however, it may bring a source of bias into the research which needs to be discussed in the interpretation of the interview when the feasibility study is written up [36]. The participants will be asked to discuss their experience and acceptability of the randomization process, the group-based PFMT, the UI outcome measure which is proposed for use in the future trial and their suggestions for future PFMT interventions. Discussion between participants will be encouraged. The consent for the interview will be obtained along with the consent for participating in the programme.

The semi-structured interview with the midwife aims to assess the acceptability of delivering the intervention. The midwife will be asked to discuss her experience of delivering the intervention, challenges and views of the feasibility of implementing the group-based PFMT across a larger population in Nanjing city. The interview will be conducted by the principal researcher in one office in the antenatal clinic. Both interviews will be digitally audio-recorded and transcribed verbatim.

The quantitative outcome measure will be recruitment rates and retention of participants, as well as the completion rates of UI outcome measures. The detail of outcome measures is shown in Table 1.

**Table 1 Tab1:** Details of evaluation measures

Outcome measures	Evaluation measures
Recruitment and eligibility	Number of participants recruited
	Percentage of eligible participants
	Ambiguities regarding eligibility criteria
	Reasons for ineligibility
Data collection	Numbers of missing items in the collected questionnaires
Attrition	Rates of dropout
Resources needed to complete the study and the intervention	Length of time required for participants to complete questionnaires, interviews and exercise diary
Participant adherence	Numbers of attended sessions
	Numbers of exercise at home
Participants’ acceptability and satisfaction with intervention	Reasons for poor attendance
	Experience of attending the intervention

Besides the outcome measures which assess the acceptability of the programme, the UI outcome measures include self-reported UI and UI severity will be assessed by ICIQ-SF (a validated questionnaire which both assesses the severity of urinary loss and quality of life impact) [37]. The adherence to the programme will be assessed by attendance records from the group-based training sessions and completion of a training diary which includes the frequency and duration the participants self-report doing the exercises. The number of PFMT exercises at home was recorded in the training diary to assess participants’ adherence to home training. The training diary will be submitted to the principal researcher after the training sessions.

The UI outcome measure has been reviewed and approved by stakeholders (phase 1) and will take a total estimated completion time of 5–10 min on each occasion. Baseline outcome measures include demographics (name, date of birth, education level, body mass index and contact details) and will be collected after obtaining informed consent from the participants. The schedule for assessments is shown in SPIRIT figure [21] (Fig. 2).

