**Fig. 2 Fig2:**
[figure not shown]
The schedule of enrolment, interventions and assessments

For the feasibility and acceptability outcomes, the assessment and progression criteria are summarized in Additional file 4: Table S1. The progression criteria provided below are based on the evidence [38, 39], results from the systematic review by Yang et al. [24] and discussion with the stakeholders. The recruitment progression criteria to proceed with RCT was set at ≥ 50% of eligible participants consented to participate in the study in 3 months which was decided based on the findings from the survey. The retention progression criteria to proceed with RCT were set at ≥ 83% (40/48) of the participants submitting the baseline questionnaires, while ≥ 79% (38/48) of the participants submit at the first follow-up time point and ≥ 75% (36/48) of the participants submit at the second follow-up (42-day after delivery). The adherence progression criteria need to be assessed from two perspectives including ≥ 75% (18/24) of the participants complete at least 75% (3/4) of the face-to-face sessions and ≥ 75% (18/24) of the participants perform PFMT twice a day at home and record it on the training diary. The progression criteria for the acceptability and delivery of the intervention were the participants and the midwife had strongly positive views on their participation in the intervention. The feasibility study will proceed with a RCT if the above progression criteria are met. The progression criteria for proceeding with changes and stopping to proceed to a further study were provided in detail in Additional file 4: Table S1.

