### Withdrawal of the study participants

Participants may withdraw from the study at any time without giving a reason. However, the data which has been collected will be kept up to the point of withdrawal. A participant will be withdrawn if they are lost to follow-up or request to leave the study or have premature delivery before 36 weeks gestation. If the participants in the supervised training group do not attend the face-to-face sessions without a reason, they will be considered as withdrawn.

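### Intervention women who miss sessions without a reason count as withdrawn and have no described interview route beyond one in-person focus group, so their reasons may be under-represented

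*Protocol article*

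**What the plan says.** Four parts of the protocol article bear on this point.

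- **Measures, Table 1.** "Reasons for poor attendance" is listed as an evaluation measure under participants' acceptability and satisfaction. No method of collection is attached to it.
- **Measures, text.** There is one focus group with participants and one interview with the midwife; these "will be held by the principal researcher in an office in the antenatal clinic". On the focus group: "About six to eight participants will be purposively sampled from the intervention groups". The sample is meant to include "both women who strongly adhered to the training programme and women who did not attend at least three face-to-face sessions". On consent: "The consent for the interview will be obtained along with the consent for participating in the programme".
- **Withdrawal of the study participants.** If women in the supervised group "do not attend the face-to-face sessions without a reason, they will be considered as withdrawn". For withdrawn participants, "the data which has been collected will be kept up to the point of withdrawal". The number of missed sessions that triggers the rule is not given. Nor does the section say whether a woman withdrawn in this way may still be interviewed.
- **Progression criteria (Measures, after Fig. 2).** Attendance passes if "≥ 75% (18/24) of the participants complete at least 75% (3/4) of the face-to-face sessions". Acceptability passes if participants and the midwife hold strongly favourable views of taking part.

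**The concern.** The withdrawal rule selects on the very thing the study wants to learn. Among women with low attendance, it takes out those whose reasons are unknown, while the Measures section sets out to hear from low attenders. If the rule is applied and withdrawn is read as no further contact, the study can establish that attendance fell short without learning why from the women least likely to have said.

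Two decisions depend on this. Acceptability is one of the criteria for going on to the full trial, and the focus group is the only described interview through which participants' views are gathered. If women who stopped coming without explanation are absent, the error runs towards proceeding. The Discussion also says that methods will be modified where qualitative or quantitative indicators show problems. If attendance misses its threshold, those modifications would rest on the accounts of women who attended or who explained their absence.

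**Working it through.** **1. The article's own figure.** Adherence threshold: 18/24 = 0.75, with 3/4 = 0.75 of sessions per woman. Both reproduce exactly.

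**2. How many women are low attenders.**
- Criterion just met: 24 − 18 = 6 women with fewer than three sessions (6/24 = 25%). If it is met with room to spare there are fewer; if it is missed there are more.
- The Sample size section cites attrition of 8.57% to 53.33% in group-based training. Applied to one arm: 24 × 0.0857 = 2.06, about 2 women, and 24 × 0.5333 = 12.80, about 13 women. Using attrition as a stand-in for low attendance is an assumption, made only to show a range.

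**3. Which of them the withdrawal rule reaches.**

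| Woman in the intervention arm | Sought for the focus group as a low attender? | Withdrawn by the rule? |
|---|---|---|
| Fewer than three sessions, reason given | Yes | No |
| Fewer than three sessions, no reason | Yes | Yes, or depends on how many missed sessions count |
| Three sessions, the one absence unexplained | No (counted as adherent) | Unclear |

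Only the second row creates the problem. The third shows that the trigger needs a number. On the narrowest reading only women who attend nothing are withdrawn. On the widest, a single unexplained absence is enough, and a woman could be both adherent and withdrawn.

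**4. Size of the affected group.** Let u be the share of low attenders whose absence is unexplained, and suppose the rule is applied to all of them. Women affected = (low attenders) × u.
- With 6 low attenders: u = 0, 0.5, 1 gives 0, 3, 6.
- With 13: u = 0, 0.5, 1 gives 0, 6.5, 13.

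The document gives no value for u. It also gives no basis for the chance that an invited woman comes to a focus group, so no probability of her presence can be derived.

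**5. Other routes to their views.** None is described for participants: no individual, remote or exit interview. The midwife's interview concerns delivering the programme. The focus group takes 6 to 8 of 24 women (25% to 33%) in one sitting. There are 24/8 = 3 training groups, so one sitting need not coincide with each woman's clinic day.

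**The case against.** A reader might infer that the focus-group plan and the withdrawal rule cannot both be followed, or that the women who know why attendance fails are likely to be missing. The document supports neither.

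- The rule covers only absence without a reason. Low attenders who explained themselves are not withdrawn by it, can be sampled, and also know why attendance fails.
- Being counted as withdrawn is not stated to bar an invitation, and interview consent is already in hand from entry.
- Under Interventions, sessions fall on the day of the regular antenatal check, a choice made to avoid extra visits. A woman who skips a session may still be in the clinic, so an in-person meeting need not mean another journey.
- Table 1 does not tie reasons for poor attendance to the focus group. The wording of the withdrawal rule itself implies that some reasons become known when sessions are missed.
- The article samples low attenders on purpose and concedes that purposive sampling may bring bias.

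All of this stands, and it confines the point to unexplained non-attenders and to the word may. It does not remove the point. Selecting a woman does not secure her presence. The conceded bias concerns the researcher's choice of participants, not removal by another rule. Consent at entry does not settle the standing of someone later classed as withdrawn. Reasons collected when sessions are missed are, by definition, not available for the women the rule withdraws. A condensed article may well leave the topic guide to the full protocol, but here it states a rule whose effect on a stated measure is left unresolved.

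**Conclusion.** The point holds in a limited form. The sections can both be followed, but they leave open whether intervention women withdrawn for unexplained absence can still be interviewed, and how many missed sessions make them withdrawn. With only one in-person group described, these women may be under-represented and acceptability may read too favourably.

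Low attenders number 6 of 24 if the attendance criterion is just met, and about 13 of 24 if low attendance matched the highest cited attrition. The unexplained part could be anywhere from none to all of them. The direction of bias assumes that women who stop coming without explanation are less favourable to the programme than those who stay, which is plausible but not shown in the document. The harm also depends on withdrawn being applied as an end to contact. This is a cheap clarification that protects a progression criterion; it is not a flaw that invalidates the design.

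**What to change.** 1. Reconcile Measures with Withdrawal of the study participants. State that stopping attendance is recorded as non-adherence and does not end study participation or availability for interview unless the woman withdraws consent. This makes a missed-session trigger for withdrawal unnecessary. The right to leave at any time without explanation is unchanged.
2. Offer every woman with fewer than three sessions a brief individual phone interview as an alternative to the focus group. Contact details are already collected at baseline, and telephoning is already used at recruitment. Make the call after the 36-week session, so that it cannot prompt the attendance being measured.
3. Report how many low attenders there were, how many were reached, and how many of those had given no reason for absence.

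Cost: at an assumed 10 minutes per call, 6 calls take 60 minutes and 13 take 130 minutes, so a few hours at most with arranging and notes. A topic-guide line and an ethics notification are also needed, but no extra staff. Downsides: recall is later than it would be straight after a missed session, these women have less group interaction, and some will still decline.

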**Fig. 2 Fig2:**
[figure not shown]
The schedule of enrolment, interventions and assessments

For the feasibility and acceptability outcomes, the assessment and progression criteria are summarized in Additional file 4: Table S1. The progression criteria provided below are based on the evidence [38, 39], results from the systematic review by Yang et al. [24] and discussion with the stakeholders. The recruitment progression criteria to proceed with RCT was set at ≥ 50% of eligible participants consented to participate in the study in 3 months which was decided based on the findings from the survey. The retention progression criteria to proceed with RCT were set at ≥ 83% (40/48) of the participants submitting the baseline questionnaires, while ≥ 79% (38/48) of the participants submit at the first follow-up time point and ≥ 75% (36/48) of the participants submit at the second follow-up (42-day after delivery). The adherence progression criteria need to be assessed from two perspectives including ≥ 75% (18/24) of the participants complete at least 75% (3/4) of the face-to-face sessions and ≥ 75% (18/24) of the participants perform PFMT twice a day at home and record it on the training diary. The progression criteria for the acceptability and delivery of the intervention were the participants and the midwife had strongly positive views on their participation in the intervention. The feasibility study will proceed with a RCT if the above progression criteria are met. The progression criteria for proceeding with changes and stopping to proceed to a further study were provided in detail in Additional file 4: Table S1.

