### Sample size

As this is a feasibility study, formal sample size calculation has not been performed. The sample size for a feasibility study needs to meet a balance between not being too large, which may cause a burden on health professionals and participants, and also not being too small as the consent rate, attrition and sample size for a large-scale RCT need to be calculated. Based on the recommendation from the National Institute for Health Research [25], an overall sample size of 30 or greater was considered sufficient for a feasibility study. In addition, a sample size between 24 and 50 is sufficient to calculate a standard deviation of an outcome, which can then be used for a formal calculation for a full-scale RCT [26, 27]. A study by Whitehead et al. [28] developed a method for determining the best approach to calculate the required sample size for a pilot trial and found that for studies where standardized differences are large, to achieve 90% power in the main trial, the required sample size for each arm is 10. For women receiving nonsurgical therapies for incontinence, reductions of four to six points in the International Consultation on Incontinence Questionnaire-Urinary Incontinence Short Form (ICIQ-UI SF) are needed to show clinically meaningful [29]. Two further studies consider the attrition rates in group-based pelvic floor muscle training in pregnant women or postpartum women range from 8.57 to 53.33% [30, 31]. Therefore, this study aims to include a sample size of 48 participants with 24 in each arm.

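### The 42-day retention go criterion is pooled over both arms and sets no limit on differential loss after delivery

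*Protocol article*

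**What the plan says.** The Sample size section states that "this study aims to include a sample size of 48 participants with 24 in each arm". The progression criteria are in the Measures section, after Fig. 2.

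- **Retention, counted over 48:** at least 83% ("40/48) of the participants submitting the baseline questionnaires"), at least 79% ("38/48) of the participants submit at the first follow-up time point") and at least 75% (36/48) "of the participants submit at the second follow-up (42-day after delivery".
- **Adherence, counted over 24, so the intervention arm only:** at least 75% ("18/24) of the participants complete at least 75% (3/4) of the face-to-face sessions"), and at least 18/24 exercising twice a day at home and recording it in the diary.

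The study proceeds to a trial if the listed criteria are met. The amend and stop levels are left to Additional file 4: Table S1.

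The section on withdrawal adds a rule that can apply to one arm only: "If the participants in the supervised training group do not attend the face-to-face sessions without a reason, they will be considered as withdrawn". The Sample size section cites attrition of 8.57% to 53.33% in earlier group-based studies. Table 1 (dropout rates) and the Data analysis section (completion proportions) mention no split by arm.

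**The concern.** The authors use an arm-specific denominator for adherence but a pooled one for retention. With a pooled count, complete return under usual care can offset heavy loss in the intervention arm. Monthly sessions, the diary and twice-daily exercise fall on the intervention arm, as does the non-attendance withdrawal rule, so unequal loss is plausible.

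The retention rate for the group-based programme is a stated objective, and the study exists to inform a definitive trial. Loss that differs between arms can bias the comparison in such a trial, whereas equal loss of the same total size is less of a threat. A go criterion that cannot tell the two apart may be recorded as met when the design needs changing.

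**Working it through.** **Inputs from the protocol article.** 24 women per arm (Sample size); retention thresholds 40/48, 38/48 and 36/48; adherence thresholds 18/24 (Measures).

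**Stated percentages.** 40/48 = 83.3%, 38/48 = 79.2%, 36/48 = 75.0%, 18/24 = 75.0%. All agree with the text.

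**Lowest intervention-arm count that still passes.** If the control arm returns c questionnaires, the intervention arm needs at least (threshold − c). With c = 24:

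| Time point | Threshold | Intervention minimum | Lost |
|---|---|---|---|
| Baseline | 40/48 | 16/24 | 33% |
| First follow-up (about 36 weeks) | 38/48 | 14/24 | 42% |
| Second follow-up (42 days after delivery) | 36/48 | 12/24 | 50% |

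Each control loss raises the requirement by one. At 42 days, c = 23 needs 13 and c = 21 needs 15.

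**Is the limiting case compatible with the adherence criteria?** Take 24 + 24 = 48 at baseline, 18 + 24 = 42 at the first follow-up and 12 + 24 = 36 at 42 days, with 18/24 women attending three of four sessions and 18/24 meeting the home-exercise criterion. Then 48 ≥ 40, 42 ≥ 38, 36 ≥ 36, and both adherence counts equal 18. Every visible quantitative retention and adherence criterion is met, with 50% lost in one arm and none in the other.

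**Chance of meeting the 42-day criterion.** Returns are taken as independent binomials with 24 women per arm, and the true retention rates are assumptions. P(pooled) = Σ over c of P(C = c) × P(I ≥ 36 − c). The second rule adds |C − I| ≤ 6. The third requires at least 18/24 in each arm.

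| True retention, intervention / control | Pooled 36/48 | Pooled, difference ≤ 6 | 18/24 in each arm |
|---|---|---|---|
| 50% / 100% | 58% | 1.1% | 1.1% |
| 50% / 95% | 40% | 5% | 1.1% |
| 50% / 90% | 26% | 7% | 1.1% |
| 50% / 80% | 8% | 5% | 0.9% |
| 60% / 95% | 75% | 22% | 10% |
| 60% / 90% | 58% | 30% | 10% |
| 80% / 80% | 85% | 84% | 66% |
| 85% / 85% | 98% | 97% | 89% |

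These are chances for the 42-day criterion alone; the other go criteria would lower them.

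**What the added limit allows.** With I + C ≥ 36 and a difference of at most 6, the lowest intervention count is 15/24 (with 21/24 in the control arm), instead of 12/24.

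**The case against.** A reader might infer that the study can pass whenever half of the intervention arm drops out. The documents do not support that. If half the arm left early in the programme, at most 12 women could attend three sessions, and both 18/24 criteria would fail. At the first follow-up, the 14/24 case passes only if at least 18 − 14 = 4 adherent women fail to return the questionnaire. The gap is therefore mainly at 42 days, and the half-lost case also needs complete return under usual care through birth and the postpartum period.

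The burden that makes one-sided loss plausible mostly ends with the last session at about 36 weeks. This weakens the argument for a large difference arising afterwards, although a woman who attends three sessions and misses the fourth without a reason might count as both adherent and withdrawn, depending on how that rule is read.

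A reader might also infer that the imbalance would be hidden. It probably would not be. The article commits to the CONSORT extension for pilot and feasibility trials, which would normally show participant flow by arm. The Discussion says that methods will be modified if there are indicators of problems affecting retention. Nor do the documents show that differential loss is the most important question for the later trial.

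A by-arm condition in Table S1 cannot be excluded. Overall retention is also a legitimate feasibility target, and requiring 18/24 in each arm would often reject acceptable designs. These points narrow the concern. What stands is that the go rule in the text does not respond to the difference between arms.

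**Conclusion.** The point holds in a limited form, as a cheap improvement. The 42-day go criterion is pooled and does not restrict differential loss, and the adherence criteria do not reach questionnaire return after delivery. At the limit, 12/24 versus 24/24 meets all visible quantitative retention and adherence criteria. A 50% loss lies inside the 8.57% to 53.33% attrition range that the article cites, but it passes only with no control loss.

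The weakness does not depend on that extreme: at an assumed 60% versus 95%, the pooled criterion is met about 75% of the time. It fades as control retention falls (8% at 50% versus 80%). The conclusion rests on the article's text alone, on the assumed retention rates above, and on independent returns between women.

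**What to change.** Keep the pooled 36/48 threshold and add a by-arm condition at 42 days, for example a between-arm difference of no more than 6 women (6/24 = 25 points). If it is not met, the outcome is to proceed with changes, not an unmodified go. Report retention by arm at each follow-up, with the difference and its 95% CI. If Table S1 already contains a by-arm condition, state it in the text.

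No new data are needed. The cost is a slightly lower chance of meeting the 42-day criterion: about 85% to 84% if both arms truly retain 80%, against a fall from 75% to 22% at an assumed 60% versus 95%. The limit of 6 is an example for the team to settle.

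The stricter alternative of 18/24 in each arm lowers the chance at 80% in both arms to 66%. Applying the first follow-up percentage within each arm (19/24, since 0.79 × 24 = 18.96) lowers that criterion's chance from 64% to 43%. Neither is a change of wording only, and neither is needed to close the gap.
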